### Follow-up

The study duration is 5 years in the first instance, and all participants are followed up annually until the end of the study, unless they withdraw. In addition, patients commencing or switching to bDMARD or tsDMARD therapy (either at recruitment, or during the course of the study) will be followed up three and six months after the start of therapy. Ordinarily, recruiting centres endeavour to ensure that each follow-up visit takes place within ±28 days of the required time.^1^ Each follow-up visit involves the collection of clinical and patient-reported data, as per baseline. To decrease the burden for recruiting centres, follow-up data collection is designed to collect clinical data using a schedule that maps to usual clinical practice insofar as possible, although data collection can also take place at additional study-specific visits.

During follow-up participants are asked to keep diaries to record any hospital admissions, new drugs prescribed, new referrals and/or pregnancy. In female participants, in the event of a pregnancy, a supplementary questionnaire is sent, shortly after the expected date of delivery, to collect information about the pregnancy, and pregnancy outcome. If a pregnancy is reported in a study participant's partner, the questionnaire is sent to the participant to pass on to their partner, with a separate participant information sheet and consent form.

### Health economics

Health care costs are collected from three main sources: clinical records, patient diaries, and record linkage. Data is collected on the frequency and type of NHS resource use, such as hospital service use related to PsA and reflects the type and duration of inpatient stays, and the type and frequency of outpatient visits. Costs include the resource use associated with usual management of the condition, together with costs associated with treatment for serious adverse events. Quality of life data will be collected from patient questionnaires, determined by the EQ-5D-5L, which enables direct calculation of quality-adjusted life years (QALYs).

### Safety

Serious adverse events are defined as per the NIHR Clinical Trials Toolkit (www.ct-toolkit.ac.uk/glossary), i.e. any event that results in death, is life threatening, requires hospitalisation or prolongation of existing hospitalisation, results in persistent or significant disability or incapacity, or is a congenital anomaly or birth defect. In addition, information on various events of special interest is collected. These events, listed in Table 4, while not necessarily constituting serious adverse events are of particular clinical interest and warrant additional data collection.

**Table 4 Tab4:** Events of special interest

Event of special interest	Further explanation
Aplastic anaemia, pancytopenia, serious neutropenia	–
Cerebrovascular accident	Stroke and/or transient ischaemic attack.
Demyelination, optic neuritis	–
Mental health	≥1 new prescription for depressive illness and/or ≥ 1 new prescription for anxiety/nervousness.
Hepatitis B reactivation	–
Hypersensitivity reaction	Including skin eruptions and rashes, oedemas, anaphylactic reactions, and non-specific hypersensitivity – e.g. Stevens Johnson syndrome, erythema multiforme, toxic epidermal necrosis. Life-threatening anaphylactoid reactions including effects on blood pressure and respiratory effects as defined for anaphylaxis [21].
Inflammatory bowel disease	Worsening of existing condition, or new onset.
Lymphoproliferative malignancy	–
Malignancy, skin cancer, Bowen’s disease	Including solid tumours, haematological tumours, melanoma, and non-melanoma skin cancers.
Major adverse cardiovascular events	Including all incident myocardial infarctions and acute coronary syndrome. Sudden cardiac death, death due to myocardial infarction, heart failure, stroke and other cardiovascular causes; myocardial infarction and non-fatal stroke.
Pregnancy	–
Psoriasis flare	Worsening of existing psoriasis, or paradoxical psoriasis onset.
Pulmonary embolism	–
Serious congestive heart failure	–
Infection	Serious infection – i.e. infection resulting in death, or is life threatening and/or requiring hospitalisation and/or intravenous antibiotics. Systemic candida infection, and all recurrent candida and other fungal infections.
Serious hepatic dysfunction or failure	–
Serious lower GI ulcer, bleed or perforation	–
Serious lupus, or lupus-like illness	–
Serious haemorrhage	–
Suicide behaviours	Including suicide ideation, suicide attempt, and suicide.
Tachyarrhythmia	Including atrial fibrillation and flutter, supraventricular tachyarrhythmia and tachycardia, and ventricular tachycardia, fibrillation, and flutter.
Tuberculosis	–
Vasculitis	Including renal and nodular vasculitis, polyarteritis nodosa, temporal arteritis, and all other vasculitis conditions.

### Biobank

Recent evidence suggests that different PsA phenotypes may be determined by distinct genotypes and cytokine responses [22]. This gives rise to specific testable hypotheses about treatment response among patients receiving therapeutic agents that ostensibly target single pathways. Not available from the start of the study, but beginning in 2021, we will collect and store urine, serum, and plasma from a sub-sample of participants to create a PsA biobank which will facilitate analyses at the genomic, epigenetic, transcriptomic (including non-coding RNA species) and metabolomics level.

Depending on local facilities, participants commencing bsDMARD or tsDMARD therapy (either at recruitment, or during follow-up) will be given the option of contributing to a biobank. Those who consent will be asked to give blood and urine samples at their normal clinical visit when commencing therapy, and at three-month follow-up. Blood samples will be centrifuged in local facilities and plasma and serum extracted, and samples will be transferred to the NHS Grampian Biorepository where they will be stored for up to 10 years.

### Statistics and data analysis

The study is designed to answer a series of questions related to natural history, outcome, treatment effectiveness and co-morbidities and is therefore not powered on one single analysis. Thus, the following are provided to give an indicative example of study power. Available data suggest that baseline risk of serious infection (infection resulting in hospitalisation, intra-venous antibiotics, or death) is around 20 events per 1000 person-years. To detect a doubling in risk among PsA patients in the exposed versus non-exposed groups we would require 1626 person-years of follow-up in each group. This would provide 90% power at 5% significance and thus, assuming a one-to-one ratio of patients, would require 723 PsA patients per group, each followed-up for an average of 3 years.

The likelihood of achieving a positive treatment response varies between products, and between outcome measures. Based on three commonly used outcomes (the ACR 20/50/70) and three commonly used agents (etanercept/infliximab/adalimumab) the average treatment response is approximately 40% [23]. Thus, assuming the probability of achieving a positive treatment response is 0.40, a sample of this size would have 90% power to detect a 50% increase in the probability of positive treatment response associated with any exposure occurring with a prevalence of 10%.

Initial analyses will consist of comparisons in baseline characteristics between exposed and non-exposed groups. Thereafter, because the study is designed to be able to answer a number of different research questions, the precise analysis will depend on the specific question being asked. All analyses will require a detailed analysis plan to be specified in advance. As indicative example: differences in risk of serious infection between groups will be examined using Cox-proportional hazards regression, allowing for between-group differences as potential confounders and effect modifiers, and results will be expressed as hazard ratios. Depending on the incidence of the outcome events, more sophisticated models may be possible – e.g. allowing the examination of time-varying and/or age-specific risks. In addition, different assumptions will be tested concerning specific risk windows. Treatment success would be pre-specified – e.g. achieving minimal disease activity twelve months after commencing treatment [24] – and initial differences in treatment outcome between exposed and non-exposed groups would be examined with simple descriptive statistics. Thereafter, a logistic model would be fitted to estimate the odds ratio for minimal disease activity between exposed/non-exposed patients. The model would be statistically adjusted for other exposures and patient characteristics associated with both the primary exposure and the outcome, to control for potential confounding.

The study will also provide several health economic outputs: firstly, descriptive statistics in terms of costs and quality of life for the entire registry population – e.g. mean/median costs and EQ-5D-5L values per patient, for first and subsequent years of treatment; and secondly, cost and QALY estimates per patient, controlling for patient differences in disease severity, number and type of adverse events, and other important potential confounding variables. Both costs and quality of life data will be estimated using regression analysis, to control for between patient differences in disease severity, number and type of serious adverse events, and other important confounding variables. Direct estimation of costs and quality of life using large-scale real-world patient data will allow us to produce more estimates of cost-effectiveness. Such results will be able to inform input parameters for future model-based economic evaluations on the costs and effects of all new treatments for PsA in the longer-term.

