All pharmacological interventions may be associated with adverse side effects. Of particular relevance, immunosuppressive therapy is considered a potential risk factor for both malignancy and life-threatening infection – although, in clinical practice, these small risks are accepted if the potential patient benefit is proportionately greater. Adverse events occurring frequently, and early during therapy, will be ascertained during phase 2 and 3 clinical trials. However, longer-term complications such as malignancy, rare infections, and indeed all rare events, are unlikely to be detected until large numbers of patients have been treated and followed for a reasonable length of time. Although much can be learned about drug safety from other disease areas, direct extrapolation from one disease to another may not be appropriate, particularly where comorbidities vary between diseases. Also, while real-world data on TNF antagonists has been available for around 20 years, much less is known about newer therapies: the IL-12/23, IL-17A, JAK and PDE4 inhibitors. Informed prescribing of new agents (and arguably new versions of old agents) requires knowledge of the magnitude of risk of adverse events in the longer-term.

Here, we describe the protocol for the British Society for Rheumatology Psoriatic Arthritis Register (BSR-PsA), a multi-centre registry facilitating research on patients with PsA, in secondary care in the Great Britain, who are commencing biologic or other targeted synthetic disease modifying anti-rheumatic drugs (bDMARDs and tsDMARDs), plus a comparison cohort of patients naïve to bDMARD / tsDMARD therapy. It aims to provide high quality long-term data on effectiveness, cost-effectiveness, safety, and the impact of PsA on the individual, including function, quality of life and social (e.g. work) outcomes in the medium- to long-term. It also collects the relevant data to allow robust health economic evaluation and post-marketing surveillance of biologic and other targeted therapies for a period beyond that typically monitored in clinical trials.

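### The cost and QALY regressions are to adjust for adverse events as confounders; if used to compare treatments, they would drop the part of incremental cost and QALY that runs through those events

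*Protocol article*

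**What the plan says.** The health-economic part of Statistics and data analysis (Protocol article) lists two outputs. The first is descriptive: costs and EQ-5D-5L values for the whole register. The second is per-patient cost and QALY estimates, "controlling for patient differences in disease severity, number and type of adverse events, and other important potential confounding variables". The next sentence repeats the rule for the regressions themselves: "to control for between patient differences in disease severity, number and type of serious adverse events, and other important confounding variables". In both places the word other puts adverse events among the confounders. Two uses follow: "Direct estimation of costs and quality of life using large-scale real-world patient data will allow us to produce more estimates of cost-effectiveness", and then "Such results will be able to inform input parameters for future model-based economic evaluations".

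Three other parts of the article bear on this:

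- Health economics: the cost outcome covers usual management "together with costs associated with treatment for serious adverse events".
- Background: "immunosuppressive therapy is considered a potential risk factor for both malignancy and life-threatening infection".
- Data collection: clinical staff report significant morbid events during follow-up, that is, after entry.

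**The concern.** A confounder is a common cause of treatment and outcome, so it must precede treatment. An adverse event during follow-up comes after treatment start and may be caused by it. It lies on the path from treatment to cost and to QALY. Holding it fixed compares patients as if the therapies had produced the same events.

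A cost-effectiveness comparison needs the total incremental cost and the total incremental QALY. A treatment coefficient adjusted for events leaves out the share that runs through them, so a therapy that causes more costly and harmful events looks cheaper and better than it is. Unlike sampling error, this does not shrink as the register grows. It matters here because the article gives open questions about long-term safety and cost-effectiveness as reasons for the register.

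**Working it through.** **No figure to reproduce.** The article gives no cost, utility or cost-effectiveness figure. The check therefore has two parts: the role of the variable, and an illustration of size.

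**Role of the variable.**

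1. Timing: events are reported during follow-up, so they come after treatment start.
2. Cause: the Background treats malignancy and life-threatening infection as possible consequences of therapy. Statistics and data analysis takes serious infection as an outcome of exposure in its Cox example.
3. Effect on the outcome: the treatment of serious events is part of the cost outcome, and such events can be expected to lower EQ-5D-5L.
4. Contrast within the article: the logistic model for treatment success adjusts for characteristics related to both exposure and outcome, which is a confounder rule. The cost and QALY models instead name events that can follow exposure.

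Nothing in the article limits the adjustment to events before treatment, or says that event-related costs and utility losses are added back.

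**Algebra.** Suppose cost = a + b·T + g·S + c·A + error, with T treatment, S baseline severity, A the event count, and d the difference in mean A between groups. The total incremental cost is b + c·d. The coefficient of T with A in the model is b. The part removed is c·d, and the same holds for QALY. This assumes an additive model with no interaction.

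**Illustration, serious infection only.** From the article's power example:

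- rate 20 per 1000 person-years in the non-exposed = 0.02 per year
- doubled in the exposed = 0.04 per year
- average follow-up 3 years

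d = (0.04 − 0.02) × 3 = 0.06 extra events per exposed patient.

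The unit costs and QALY losses below are assumptions. A least-squares check used 400,000 simulated patients per scenario, Poisson event counts, treatment independent of severity, and an assumed direct effect of 15,000 cost units and 0.15 QALY.

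| Assumed per event | Removed, 0.06 × value | Simulated cost difference: without / with event term | Simulated QALY difference: without / with |
|---|---|---|---|
| 2,000 units; 0.02 QALY | 120; 0.0012 | 15,120 / 15,002 | 0.1489 / 0.1501 |
| 5,000 units; 0.05 QALY | 300; 0.003 | 15,296 / 14,998 | 0.1469 / 0.1499 |
| 10,000 units; 0.10 QALY | 600; 0.006 | 15,593 / 15,000 | 0.1441 / 0.1500 |

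In each scenario the adjusted coefficient returns to the direct effect, so the whole event-mediated part is lost. In the middle row the shift is 300 / 15,300 ≈ 2% for cost and 0.003 / 0.147 ≈ 2% for QALY. Both shifts favour the treatment with more events. The percentages depend on the assumed direct effects.

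**The case against.** The strongest reply is that the health-economic text names no treatment coefficient, no exposed versus non-exposed cost difference and no incremental ratio, whereas the effectiveness example does name its contrast. This stands in part. A reader might infer that the register's cost-effectiveness result will necessarily lose its safety costs. The documents do not go that far: the loss occurs only if the adjusted estimate is read as an incremental quantity. Still, calling a variable a confounder has meaning only relative to a contrast, and cost-effectiveness is the first stated use.

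Second, estimates conditional on events are proper inputs to a decision model that enters event rates separately; including event costs in its base estimate would count them twice. This stands, and it is why the adverse-event terms should move to a separate model and not be dropped altogether. For the same reason, a reader might see a contradiction between the Health economics section and the regression text, but there is none: regressing a cost that includes event treatment on the events is how an event-specific cost is estimated.

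Third, the descriptive means and medians keep event costs. True, but they do not control for differences between groups in who receives therapy.

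Fourth, the article requires a detailed plan in advance for every analysis. That plan could correct the matter, for instance by averaging predictions over each group's own event distribution. But the covariate rule is stated here, twice, and a plan that followed it would inherit the problem.

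Two further inferences are only conditional. Adjusting for disease severity would remove treatment benefit if severity were measured during follow-up; the text does not date it, and severity is collected at baseline too. Conditioning on events may also open bias through shared causes of events and costs, but the documents give no means of judging this.

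**Conclusion.** The point holds in conditional form. The article classes adverse events as confounders in regressions meant to yield cost-effectiveness estimates, while treating such events elsewhere as possible effects of therapy and counting the treatment of serious ones as cost. Any treatment comparison read from those models would omit the event-mediated part of incremental cost and QALY, and the error would favour the therapy that causes more events.

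The size cannot be computed from the documents. For serious infection alone, if the doubling in the power example occurred, it would be 120 to 600 cost units and 0.0012 to 0.006 QALY per patient over 3 years, about 2% of the difference in the central example. This rests on assumed unit values, assumed direct effects and an additive model. The doubling is a power scenario, not an expected result. Other event types would add to or offset this, depending on whether therapy raises or lowers their rate. A claim of large bias is not supported; a claim that the covariate rule is wrong for treatment comparisons is.

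**What to change.** State that any cost or QALY model used to compare treatments, or exposed with non-exposed patients, adjusts only for variables measured at or before treatment start: baseline severity, baseline EQ-5D-5L, comorbidities and history of events before that date. Adverse events during follow-up should not be covariates in these models.

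Keep a separate model with adverse-event terms to estimate event-specific costs and utility losses as decision-model inputs. Say that its treatment coefficient is not the total incremental effect.

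The cost is a change of wording in the protocol and the analysis plan, and one additional regression. No new data are needed.

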### Research governance and study oversight

The study was externally peer reviewed as part of the process of applying for funds, competitively, to the British Society for Rheumatology (BSR) and is registered on the Open Science Framework (https://osf.io/jzs8n). Favourable ethical opinion, which applies to all sites, was obtained from the NHS West of Scotland Research Ethics Committee 3 (reference: 18/WS/0126). Appropriate NHS Research and Development approval is obtained prior to the commencement of participant recruitment at each site. The BSR is the legal sponsor for the study, but delegates certain functions to the University of Aberdeen.

The study is co-ordinated by a Study Management Group consisting of the study investigators. A study co-ordinator oversees the study and is accountable to the Chief Investigator. A Data Monitoring Committee is convened by the BSR. The register and data belong to the BSR and oversight of the BSR-PsA is undertaken by the BSR Registers Committee, consisting of BSR members with various other co-opted representatives including the Chief Investigator and Deputy Chief Investigator of the BSR-PsA, patient organisation representatives, and representatives from the BSR’s other registers. Separately, and reporting to the BSR Registers Committee, a Data Monitoring Committee reviews reports of all serious adverse events and events of special interest.

### Dissemination of findings

Dissemination of research output from the BSR-PsA will comply with the policy as specified by the BSR’s Registers Committee. In addition, for output from the main study investigators, lay summaries will be made available online.

## Discussion

Various extant registers across Europe collect some data on PsA, including industry-sponsored and independent registers, but the utility of these data is limited. The BSR Biologics Register for Rheumatoid Arthritis (BSRBR-RA) [25] initially included some patients with PsA although with a predominant focus on rheumatoid arthritis failed to adequately capture all relevant domains in PsA, especially skin disease and information on PsA-relevant outcomes is limited (for example, by using DAS28, rather than full 66/68 joint counts, and no assessment of axial disease. Also, being outside their initial remit, when numbers of patients with rheumatoid arthritis increased, recruitment on PsA ceased. In other registers, such as the British Association of Dermatologists Biologic and Immunomodulators Register (BADBIR) [26], although skin disease is well characterised, the full clinical features of PsA are poorly documented (rheumatological assessment is limited to the single question: Has the patient received a diagnosis by a rheumatologist of psoriatic arthritis?).

There is clear evidence, from randomised trials, that bDMARDs and tsDMARDs are efficacious in the treatment of PsA [23, 27, 28]. However, it has been shown that certain clinical (e.g. oligoarthritis, those with comorbidities) and sociodemographic groups are likely to be under-represented in clinical trial populations [29], and this is likely to introduce potential bias to absolute effect estimates. Indeed, data from the BSR Biologics Register for Ankylosing Spondylitis indicate that in a real-world patient population around half of patients respond to TNF inhibition [6], compared to > 60% in the clinical trials that led to the licensing of these agents. Also, there is some evidence from a large claims database in the USA that the majority of patients commencing TNF or IL-12/23 inhibition had continued their index therapy within a twelve-month period [30]. Long-term studies have the opportunity to examine effectiveness of these agents in real-world clinical populations and allows the examination of patient sub-groups that are seldom available in clinical trials.

The broad inclusion criteria for the exposed group, allowing patients commencing any bDMARD or tsDMARD, is deliberately inclusive to reflect real-world practice. The advent of biosimilars has brought a rapid increase in the number of alternative bDMARDs available to the rheumatologist. Although manufactured to be ‘similar’ to the originator product, and non-inferior in terms of effectiveness and safety profile, biosimilar molecules are not required to be tested in all indications and, subsequently, may be licenced for use in PsA without any clinical trial data in this patient group. Real-world data therefore serve an important function in monitoring effectiveness, safety, and cost-effectiveness of these new products.

Previous economic modelling in PsA, on which management guidelines are based, have employed mapping techniques to estimate quality of life as a function of disability and skin disease [31]. While these indirect methods have some merit, where direct measurement of health utility is lacking, there is some evidence that health utility scores obtained by extrapolating from disease activity and function differ markedly from those calculated directly [32]. Large-scale real-world patient data are required with estimates of QALYs determined using directly collected health economic measures, as well as the clinical tools used elsewhere. This will permit robust estimates of cost-effectiveness and will either challenge or confirm the indirect methods used in economic modelling to date.

In summary, we have described the rationale and design for a prospective PsA registry to provide real-world data with respect to the natural history of PsA and the impact on the individual, including function, work, and quality of life in the medium- to long-term; and the use of effectiveness, cost-effectiveness, and predictors of treatment response of bDMARD and tsDMARD therapeutics. Further, reserving biological samples against an extensive clinical phenotyping database future-proofs the BSR-PsA and facilitates biomarker evaluation and predictive modelling using various mathematical and informatics solutions.

